# Digital Cognitive Behavioural Therapy for Insomnia versus sleep hygiene education: the impact of improved sleep on functional health, quality of life and psychological well-being. Study protocol for a randomised controlled trial

**DOI:** 10.1186/s13063-016-1364-7

**Published:** 2016-05-23

**Keywords:** Insomnia, Sleep, CBT, Digital, Health, Function, well-being

## Abstract

**Background:**

Previous research has demonstrated that digital CBT (dCBT), delivered via the Internet, is a scalable and effective intervention for treating insomnia in otherwise healthy adults and leads to significant improvements in primary outcomes relating to sleep. The majority of people with insomnia, however, seek help because of the functional impact and daytime consequences of poor sleep, not because of sleep discontinuity per se. Although some secondary analyses suggest that dCBT may have wider health benefits, no adequately powered study has investigated these as a primary endpoint. This study specifically aims to investigate the impact of dCBT for insomnia upon health and well-being, and will investigate sleep-related changes as mediating factors.

**Methods/design:**

We propose a pragmatic, parallel-group, randomised controlled trial of 1000 community participants meeting criteria for insomnia disorder. In the DIALS trial (Digital Insomnia therapy to Assist your Life as well as your Sleep), participants will be randomised to dCBT delivered using web and/or mobile channels (in addition to treatment as usual (TAU)) or to sleep hygiene education (SHE), comprising a website plus a downloadable booklet (in addition to TAU). Online assessments will take place at 0 (baseline), 4 (mid-treatment), 8 (post-treatment), and 24 (follow-up) weeks. At week 25 all participants allocated to SHE will be offered dCBT, at which point the controlled element of the trial will be complete. Naturalistic follow-up will be invited at weeks 36 and 48. Primary outcomes are functional health and well-being at 8 weeks. Secondary outcomes are mood, fatigue, sleepiness, cognitive function, productivity and social functioning. All main analyses will be carried out at the end of the final controlled follow-up assessments and will be based on the intention-to-treat principle. Further analyses will determine whether observed changes in functional health and well-being are mediated by changes in sleep. The trial is funded by Big Health Ltd.

**Discussion:**

This study will be the first large-scale, specifically designed investigation of the health and well-being benefits of CBT for insomnia, and the first examination of the association between CBT-mediated sleep improvement and health status.

**Trial registration:**

ISRCTN60530898.

**Electronic supplementary material:**

The online version of this article (doi:10.1186/s13063-016-1364-7) contains supplementary material, which is available to authorized users.

## Background

### The importance of insomnia

Insomnia disorder comprises a complaint of poor sleep, with associated significant daytime effects, occurring at least 3 nights per week for at least 3 months [1]. Worldwide, epidemiologic studies report the prevalence of a chronic clinical insomnia disorder at 10 to 12 % [2–4]. Although prevalence is high, natural remission is low. In one study, 74 % of those with insomnia continued to have insomnia a year later and 46 % reported insomnia persisting for over 3 years [5]. Traditionally considered as ‘secondary’, subsumed as symptoms of other clinical diagnoses within mental health care, the recently revised *Diagnostic and Statistical Manual of Mental Disorders, version 5* (DSM-5) outlines the ‘need for independent clinical attention of a sleep disorder’ (p. 1) [1]. This is supported by research demonstrating not only that rates of mental and physical health co-morbidity are high, but that pre-existing chronic insomnia is an independent risk factor for development of depression [6], cardiovascular disease [7] and type 2 diabetes [8, 9]. From the standpoint of public health and well-being, sleep appears to be a more important matter than has been hitherto recognised [10, 11].

### The relationship between poor sleep, daytime functioning and quality of life

Typically, insomnia is associated with increased fatigue, impaired work productivity, reduced quality of life and relationship satisfaction, as well as increased ill-health [12–14]. Despite such evidence of poor functioning being attributed to poor sleep, and also being an essential diagnostic criterion for insomnia, there has been comparatively little research on quality of life. This is all the more surprising given that the perceived impact on personal functioning serves as an important driver of complaint and of help-seeking behavior rather than simply perceived sleep loss [15, 16]. In one large epidemiological study, four of the five most commonly cited reasons for seeking a sleep consultation with a health professional, were daytime consequences of fatigue, psychological distress, physical discomfort, and reduced work productivity [16]. Clinician reports of patient consultations, and cross-sectional and prospective questionnaire studies [17, 18] further demonstrate that individuals with insomnia complain of deficits in mood and cognitive abilities (concentration, memory, attention), coupled with elevated levels of anxiety, fatigue and physical pain/discomfort. Thus, once a threshold of noticeable effect on one’s life is reached, such individuals may feel motivated to seek medical advice.

### Cognitive behavioural therapy (CBT) for insomnia

CBT, regarded as the treatment of first choice for persistent poor sleep [19–21] is a psychological treatment designed to break the patterns of maladaptive thinking and behaviour that serve to maintain insomnia. CBT comprises a range of techniques including a behavioural component (stimulus control, sleep restriction, relaxation) combined with a cognitive (managing sleep-related worries, the racing mind and intrusive thoughts) and an educational (sleep hygiene) component. Meta-analyses indicate that CBT has moderate to large and durable effects on sleep quality, sleep efficiency, sleep onset latency and wake time after sleep onset [22–24]. Moreover, approximately 60 % of those who receive CBT respond to treatment and 39 % achieve remission [25]. What is much less well-established is the effect that CBT may have upon the daytime symptom and functional health profile of people with insomnia. Logically, effective treatment should alleviate such impairments; and furthermore, based on the evidence that impaired sleep may be causally related to reduced quality of life domains (well-being and impaired daytime functional status), improving sleep should improve functioning. There is some preliminary evidence from secondary analyses that CBT may yield generalised benefits [26–29], and even some primary data in small samples that CBT for insomnia may reduce depressive or anxiety symptoms [30, 31], but an adequately powered, definitive trial examining functional health status and well-being is long overdue.

### The current study

This study seeks to ascertain the impact of improved sleep on three key areas of quality of life: functional health status, patient-generated (sleep-related) quality of life impairment and psychological well-being. Over the past 5 years, self-help CBT delivered via the Internet has been introduced, not least because of the importance of widening access to effective psychological therapy. Several randomised controlled trials (RCTs) have evaluated digital CBT (dCBT) applications; each of which has found moderate to large improvements in insomnia symptoms relative to waitlist groups [32–34]. Only one programme, however, has been tested versus a placebo intervention, demonstrating significant and sustained improvements in sleep continuity; for example, sleep diary-assessed sleep efficiency, sleep onset latency and wake time after sleep onset, and self-reported global sleep quality [34]. It is this dCBT intervention that will be used in the present study. Data from the programme show that more than 80 % of participants complete the course within 8 weeks.

The primary hypotheses for the trial are that, compared to sleep hygiene education (SHE):The dCBT intervention will be associated with improved functional health status by the end of treatment (8 weeks)The dCBT intervention will improve positive psychological well-being by the end of treatment (8 weeks)The dCBT intervention will be associated with reduced patient-generated sleep-related quality of life impairment (8 weeks)The effect of dCBT on outcomes (8 weeks) will be mediated by sleep status during the treatment phase (4 weeks)

The secondary hypotheses are that, compared to SHE:The dCBT intervention will be associated with reduced symptoms of negative mood, fatigue and relationship/social dysfunction by the end of treatment (8 weeks)The dCBT intervention will be associated with reduced problems with sleepiness, cognitive impairment and productivity by the end of treatment (8 weeks)Improvements will be maintained at follow-up (24, 36, 48 weeks)The effect of dCBT on longer-term outcomes (24, 36, 48 weeks) will be mediated by sleep status during and upon completion of the treatment phase (4, 8 weeks)

## Methods/design

### Research design

The study is a parallel-group, superiority, RCT of dCBT (+ treatment as usual, TAU) versus SHE (+TAU). The trial design is summarised in Fig. 1. The study will be carried out completely online. Participants will access the screening assessment, participant information statement, informed consent form, allocation to condition and intervention, and baseline and follow-up assessments via web or mobile platforms (see also Additional files 1 and 2). Participants will be able to print a copy of the participant information statement and will have the opportunity to contact the researchers via phone or email before consenting. The study has received ethical approval from the University of Oxford Medical Sciences Inter-Divisional Ethics Committee (ref MS-IDREC-C2-2015-024) and is registered at ISCRTN (ISRCTN60530898).

**Fig. 1 Fig1:**
[figure not shown]
Summary of the trial design for the Digital Insomnia therapy to Assist your Life as well as your Sleep (DIALS) study. *SCI* Sleep Condition Indicator, *dCBT* digital cognitive behavioural therapy, *SHE* sleep hygiene education

### Participants

We will recruit 1000 community participants. Our inclusion criteria comprise: (1) a positive screen for probable DSM-5 insomnia disorder, (2) a test score of ≤ 16 on the Sleep Condition Indicator (SCI) [35], (3) being aged 18 or older (no upper age limit), (4) having reliable Internet access at home or at work, and (5) being able to read and understand English. We will screen for co-morbid conditions and medication use at baseline but exclude only those people whose health may be considered to be unstable such as significant current symptoms of (a) an additional sleep disorder (e.g. excessively sleepy and possible obstructive sleep apnoea), (b) psychosis or mania, (c) serious physical health concerns necessitating surgery or with a prognosis less than 6 months, (d) those undergoing a psychological treatment programme for insomnia with a health professional, and (e) habitual night shift, evening, or rotating shift-workers. Information covering (a) to (e) will be gathered using online self-report questions, there will be no medical examinations or access to medical records. We will not omit participants who take medication for sleep problems, or for any other physical or mental health problems providing they report their health to be stable. The study will recruit through several channels. These may include online, print and broadcast media announcements or advertisements and the use of contact lists where adults who have volunteered to be involved in research will be re-contacted (See Additional file 3). For example, following completion of open access sleep surveys such as the Great British Sleep Survey (GBSS: www.greatbritishsleepsurvey.com or World Sleep Survey, WSS: www.worldsleepsurvey.com, which generate data on tens of thousands of respondents). Potential participants will also be alerted to the study by information placed on the Sleepio® website (www.sleepio.com) and on the Sleepio® App site (which generate data on hundreds of thousands of respondents). Participants will not receive reimbursement for their participation, but will be provided with access to the dCBT programme free of charge, regardless of allocation to experimental condition. Informed consent will be obtained from all participants.

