### Planned intervention

Digital cognitive behavioural therapy will be delivered using the Sleepio® programme [34] (www.sleepio.com and associated Sleepio® App). The programme is fully automated and its underlying algorithms feed the delivery of information, support, and advice in a personally tailored manner. Delivery is structured into six sessions, lasting an average of 20 minutes each. Certain tools (such as sleep diaries and relaxation audios) can also be accessed using the web browser of any smartphone. All of the six core sessions, sleep diaries, relaxation audios, and the scheduling tool can also be accessed using an iOS App, but this is only an option for participants who have an iPhone®. The treatment content is based on CBT for insomnia manuals [26–28] and includes a behavioural component (sleep restriction, stimulus control, and relaxation), a cognitive component (paradoxical intention, cognitive restructuring, mindfulness, positive imagery, and putting the day to rest) and an educational component (psycho-education and sleep hygiene).

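### Exclusion (d) leaves current users of the tested programme, or of another digital CBT, eligible for either arm, although the programme's own website and app are one recruitment channel

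*Protocol article*

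**What the plan says.** All references are to the protocol article.

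- **Recruitment (Participants).** "The study will recruit through several channels": media announcements or advertisements, contact lists of research volunteers, open-access sleep surveys and, in addition, the product's own pages: "Potential participants will also be alerted to the study by information placed on the Sleepio® website" and on its app site.
- **Treatment under test (Planned intervention).** "Digital cognitive behavioural therapy will be delivered using the Sleepio® programme". It is the same product, and "The programme is fully automated".
- **Exclusions (Participants).** The trial will "exclude only those people whose health may be considered to be unstable", followed by items (a) to (e), on which information is gathered by online self-report. The only item about insomnia therapy is (d): "those undergoing a psychological treatment programme for insomnia with a health professional".
- **Entry threshold (Participants).** Entrants must screen positive for insomnia disorder and score 16 or less on the SCI.
- **Care during the trial (Planned intervention).** Both arms receive their treatment on top of usual care, which nobody is required to change. Controls are offered dCBT at week 25 (Assessment points).
- **Analysis (Statistical analysis).** The primary outcomes are compared at 8 weeks by intention to treat.

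**The concern.** Criterion (d) evidently aims to keep concurrent psychological treatment for insomnia out of the comparison. As worded, it catches only treatment delivered by a professional. A self-guided user of an automated programme is not under a professional, so (d) does not apply, and such use is not a form of unstable health either. The omitted route is the treatment under test, and one recruitment channel reaches people through that treatment's own pages.

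A current user allocated to SHE could carry on with the programme. A current user allocated to dCBT would receive what he or she already has. In both cases the person adds little to the difference between arms, and the intention-to-treat estimate moves towards zero. The platform analytics are described for the dCBT group only (Outcome measures), so exposure in the SHE arm might also go unseen.

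**Working it through.** **1. Is a current user eligible?** Set the passages side by side. The programme is automated, so its user has no treating professional. Criterion (d) requires one. Items (a), (b), (c) and (e) concern other sleep disorders, psychosis or mania, serious physical illness and shift work. None applies to a person merely because he or she uses digital CBT. If the person still has insomnia and an SCI of 16 or less, the stated rules admit him or her.

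**2. Reproduce the planned size.** Inputs from Sample size calculation: significance level 1.667 %, power 90 %, standardised effect 0.25, 433 per arm analysed, 13 % dropout, 500 per arm recruited. Sidedness is not stated.

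n = 2 × (z₁₋α/₂ + z₁₋β)² / d² = 2 × (2.3940 + 1.2816)² / 0.25² = 2 × 13.510 / 0.0625 = 432.3, rounded up to 433. The two-sided reading matches exactly; the one-sided reading gives 372. With dropout, 433 / 0.87 = 497.7, or 498, against 500 planned. There is no error here, and almost no reserve: 500 × 0.87 = 435 per arm, two more than needed.

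**3. Effect of dilution.** Let f be the share of the sample made up of current users and L the fraction of the effect lost in them. Neither is in the documents; both are assumptions.

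- Diluted effect: d = 0.25 × (1 − f × L)
- Power: Φ(d × √(433/2) − 2.3940), with √(433/2) = 14.714

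Example for f × L = 10 %: d = 0.25 × 0.90 = 0.225; 0.225 × 14.714 − 2.3940 = 0.917; Φ(0.917) = 82.0 %.

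| Contrast lost, f × L | Effect (SD) | Power at 433 per arm | n per arm for 90 % power |
|---|---|---|---|
| 0 | 0.25 | 90.1 % | 433 |
| 5 % | 0.2375 | 86.4 % | 479 |
| 10 % | 0.225 | 82.0 % | 534 |
| 20 % | 0.20 | 70.8 % | 676 |

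The 5 % row is a 5 % share with full loss (L = 1) or a 10 % share with half loss (L = 0.5). The 10 % row is a 10 % share with full loss or a 20 % share with half loss. At a 10 % loss, the 534 analysed participants needed per arm already exceed the 500 to be recruited.

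These figures follow the plan's own calculation, which takes no credit for baseline adjustment. If 0.25 is in units of the unadjusted SD, the analysis of covariance would give back some power. The article states no baseline correlation, so none is credited here.

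**The case against.** The case on the other side has real weight.

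- **One channel among several.** The product's pages are listed last, and seeing a notice there is not the same as using the programme. A reader might infer that users will enter both arms. The text shows only that they can. This limit stands.
- **Past users.** Those in remission cannot pass the SCI threshold, and the article gives no ground for saying that the rest would gain nothing from repeating the course. The concern is therefore about current use; previous use is something to record.
- **Early crossover.** A reader might infer that SHE participants recruited through the product's pages are those most likely to obtain the programme before week 25. The article does not support that. Everyone is promised free access, which gives controls a reason to wait, and crossover after week 8 cannot touch the primary endpoint.
- **An open list.** The exclusions are introduced as examples, and the additional files are not shown. But the sentence restricts exclusion to unstable health, and the self-report screen is described as covering (a) to (e). An unlisted item on digital CBT would fit neither.
- **Recording of service use.** Health-care use is audited at each assessment (Outcome measures). That partly answers the monitoring point, but digital CBT is not named and a self-help user may not report it as health care.
- **A pragmatic trial with usual care in both arms.** This is a fair argument against barring everyone who ever tried self-help CBT. It does not explain why concurrent therapy from a professional is excluded while concurrent use of the tested product is not.
- **Direction.** Users are balanced between arms in expectation, so the harm is attenuation and lost power, not a false positive. This stands and limits the severity.

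**Conclusion.** The eligibility gap is real and rests on text that the article states, not on detail left to a fuller document. Current users of the study programme or another digital CBT are eligible, could enter either arm, and face no stated bar to continuing if allocated to SHE. The consequence is attenuation of the 8-week intention-to-treat contrast.

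The size is unknown. Assuming that 5 to 20 % of the contrast is lost, power falls from 90 % to about 86 to 71 %. Assuming that such users lose half the effect, a 10 to 20 % share leaves about 86 to 82 %. A more alarming figure can be produced: a 30 % share with no effect at all gives 0.175 SD and 57 % power. Nothing in the article points to such a share, so that figure should not be used as an estimate. The finding is a cheap improvement that protects the contrast; it does not show that the trial is underpowered.

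**What to change.** 1. Extend criterion (d) to current use of the study programme or any other digital CBT for insomnia. This takes one self-report screening item, checked against existing programme accounts where possible.
2. Record previous use of such programmes at baseline, without excluding on it.
3. Ask about CBT and dCBT use in both arms at weeks 4, 8 and 24, and report it by arm.
4. Add a sensitivity analysis of the primary outcomes without participants who reported previous use at baseline. Because this is a pre-randomisation characteristic, the comparison between the remaining arms stays randomised. Use during the trial should be described, not used to drop participants.

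The cost is a few questionnaire items and one look-up. The downside is that a few otherwise eligible visitors are lost and the community sample becomes slightly narrower. The loss should be tolerable, since 1000 participants are needed and the article describes the product's pages as generating data on hundreds of thousands of respondents.

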### Randomisation and allocation concealment

This study will use simple randomisation with an allocation ratio of 1:1, as recommended for large clinical trials [36]. It will be carried out by the automated online system. Hence the research team will be unable to influence randomisation, and will have no access to future allocations.

### Assessment points

Assessments will take place at weeks 0 (baseline), 4 (mid-treatment), 8 (post-treatment), and 24 (follow-up). In consideration of ethical matters, at week 25 all participants in the control group will be offered dCBT to help with their sleep problems, and so at that point the controlled element of the trial will be complete. Thereafter, there will be a naturalistic follow-up. All participants will be invited to complete further assessments at weeks 36 and 48.

### Planned intervention

Digital cognitive behavioural therapy will be delivered using the Sleepio® programme [34] (www.sleepio.com and associated Sleepio® App). The programme is fully automated and its underlying algorithms feed the delivery of information, support, and advice in a personally tailored manner. Delivery is structured into six sessions, lasting an average of 20 minutes each. Certain tools (such as sleep diaries and relaxation audios) can also be accessed using the web browser of any smartphone. All of the six core sessions, sleep diaries, relaxation audios, and the scheduling tool can also be accessed using an iOS App, but this is only an option for participants who have an iPhone®. The treatment content is based on CBT for insomnia manuals [26–28] and includes a behavioural component (sleep restriction, stimulus control, and relaxation), a cognitive component (paradoxical intention, cognitive restructuring, mindfulness, positive imagery, and putting the day to rest) and an educational component (psycho-education and sleep hygiene).

The programme is highly interactive, and content is presented by an animated virtual therapist. Participants make a time for the session and are prompted via email and/or short text message (SMS) if they do not ‘attend’. Participants complete daily sleep diary information throughout the intervention, which is used by the programme to provide tailored, personalised help. Participants receive an email and/or SMS reminder each morning to prompt them to fill in their sleep diary. In addition, participants complete a short questionnaire at the beginning of therapy to set treatment goals. Throughout the course of therapy, participants have access to a moderated online community and an online library of information about sleep. Participants can view their online case file, which includes four sections: a progress review, a reminder of strategies to try out between sessions, an agreed sleep schedule, and a list of further reading. The system provides online analytics, which can be used to monitor adherence by assessing how many sessions were completed and the number of weeks to complete the course. All information gathered for the programme will be stored in encrypted form on secure servers. Passwords are stored in encrypted form and all sensitive traffic is transmitted securely via SSL by default. Participants will have access to the intervention for up to 12 weeks. Digital CBT will in effect be dCBT + TAU because there will be no requirement for participants to alter their usual care in any way. Physicians, for example, will be free to offer appointments, to prescribe, and to maintain/discontinue prescriptions as they see fit.

Sleep hygiene education (SHE) has been selected for the control arm because this is what people with insomnia are offered most typically in routine care. To ensure consistency of approach and content, SHE will be delivered on a dedicated website where materials can be viewed and downloaded. SHE will be based on recognised sleep hygiene advice [37–39] and will comprise behavioural advice concerning both lifestyle factors and environmental factors associated with sleep and sleeplessness. The latter in particular will focus on creating the optimal bedroom environment for good sleep. The content of SHE will cover the importance of limiting caffeine, nicotine, and alcohol and of carefully managing diet and exercise (lifestyle), as well as limiting noise and light, managing room temperature and body temperature, and improving air quality and bed comfort (environment). SHE will in effect be SHE + TAU because again there will be no requirement for the usual care of participants to be altered in any way.

